#### Secondary outcomes

The secondary outcomes include three types: patient related, infection related, and surgery related.

The patient-related outcomes will include their quality of life prior to surgery, on discharge, and on POD 30, using the EuroQol 5D and SF36 questionnaires.

The principal infection-related outcome will be the proportion of patients with superficial SSIs, defined as infections that occur within 30 days of the intervention and affect the skin and subcutaneous tissues and for which at least one of the following signs is observed: pus coming from the superficial part of the incision, bacteria isolated from a liquid or tissue sample collected aseptically from the superficial part of the incision, a sign of infection (pain, tenderness, redness, burning, etc.) associated with deliberate opening of the superficial part of the incision by the surgeon (except if the culture is negative). Infection of the superficial part of the incision is diagnosed by the surgeon (or the physician attending to the patient). The definitions are based on that published by the CDC. Additional infection-related outcomes include the post-operative infection rates by POD 30, including SSIs and distant infections, the number of antibiotic-free days between randomization and POD 30, a description of the microbial flora, as found in the antibiogram of the perioperative sample that is collected in all cases, and the balance between antibiotic therapy and microbial resistance. The antibiotic treatment will be considered adequate if no bacteria are found in the perioperative sample or if all of the detected bacteria are sensitive to the administered antibiotic therapy. The antibiotic treatment will be considered inadequate if the perioperative sample is positive for resistant bacteria.

Surgery-related outcomes will include morbidity and mortality according to the Dindo-Clavien classification [25] and the CCI [26]; length of stay (LOS), defined as the number of days of hospitalization between surgery and discharge; and rehospitalization rate, defined as rehospitalization during the study period.

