#### Inclusion visit

The inclusion visit (which is the same as the screening visit) will include a physical examination, including cardiac blood flow, body temperature, and pain evaluation; a laboratory test battery (blood ion profile, ASAT, ALAT, total bilirubin, indirect bilirubin, alkaline phosphatase, GGT, amylase, lipase, CRP, hCG (if applicable), procalcitonin levels, and leukocyte count).

The laparoscopic appendectomy will then be performed, regardless of the hour or day, and the randomization performed after the appendectomy.

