#### Statistical methods

Qualitative variables will be presented as numbers (percentages) and compared using a chi-squared test with Yates’ correction or (if applicable) Fisher’s test. Quantitative variables will be presented as the means ± standard deviation or medians (interquartile range) and compared using Student’s *t*-test or a Wilcoxon signed-rank test, as appropriate. Kaplan-Meier curves for the time to event will be built and compared using a log-rank test.

A detailed statistical analysis plan will be defined and validated by the study’s scientific advisory board. Any modifications must be made before unblinding of the database and must be validated by the scientific advisory board.

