##### Analysis of secondary endpoints

The patient-related endpoint, consisting of quality of life prior to surgery, on discharge, and on POD 30 after surgery, will be assessed in a mixed model analysis of variance with a Bonferonni-Holm closed testing procedure for post hoc analyses.

In terms of the infection-related endpoints, the proportion of patients with superficial SSIs will be assessed using a chi-squared test or Fisher’s test. The post-operative infection rates by POD 30, including SSIs and remote infections, will also be assessed using a chi-squared test or Fisher’s test. The number of antibiotic-free days between randomization and POD 30 will be assessed using Student’s *t*-test or a Wilcoxon test. The microbial flora will be assessed using a chi-squared test or Fisher’s test. The proportion of patients with adequate antibiotic treatment will also be assessed using a chi-squared test or Fisher’s test.

In terms of the surgery-related endpoints, morbidity and mortality (according to the Dindo-Clavien classification) will be assessed using a Wilcoxon test, LOS will be assessed using a chi-squared test or Fisher’s test, and the rehospitalization rate will be assessed using a chi-squared test or Fisher’s test.

Statistical analysis will be performed using SAS® software (version 9.4, SAS Institute Inc., Cary, NC, USA).

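### Length of stay is a day count assigned a test for categories, the named Wilcoxon test is the paired one, and flora sampled before randomization is tested as an outcome

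*Protocol article*

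**What the plan says.** **Length of stay.** The Secondary outcomes section lists LOS, "defined as the number of days of hospitalization between surgery and discharge". The Analysis of secondary endpoints section says "LOS will be assessed using a chi-squared test" or Fisher's test. The general Statistical methods section sets the rule by type of variable: qualitative variables are "compared using a chi-squared test with Yates’ correction or (if applicable) Fisher’s test", while quantitative variables get Student's t-test "or a Wilcoxon signed-rank test, as appropriate".

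**Design.** The Trial design section describes two parallel groups randomized 1:1. No pairing or matching is described anywhere.

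**Flora and adequacy.** Both are secondary outcomes judged on the perioperative sample. The analysis section says "The microbial flora will be assessed using a chi-squared test" or Fisher's test, and gives adequacy the same tests. The Treatment administered section defines the perioperative period as the duration of anesthesia. The Inclusion visit section has "the randomization performed after the appendectomy", and the Randomization section also places it at the end of surgery. Adequacy requires a negative sample, or that every isolate be sensitive to the antibiotic therapy administered. The article does not say whether that means the drugs given to everyone up to the end of the operation or the randomized post-operative drugs.

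**The concern.** Each of these is an explicit statement in the article, not a detail left to an analysis plan that is not shown. A plan that follows the text would inherit all of them.

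- **LOS.** A chi-squared or Fisher test treats 4, 5 and 12 days as unordered labels, or needs a cut-point that is not given. It yields a p-value but no difference in days. The Discussion cites longer stays and higher costs as harms of extended antibiotic use, so this endpoint bears on the trial's rationale.
- **Signed-rank.** The test needs pairs, and the trial has none.
- **Flora.** Allocation cannot change a sample already taken. Any difference between arms is chance, and a significant one could be misread as an effect of treatment.
- **Adequacy.** Under one reading it is a baseline variable; under the other it has no sensible value in the placebo arm.

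**Working it through.** **1. The plan's own figure, for context.** Control rate 12%, margin 5 points, two-sided alpha 5%, power 80%, loss 10% (Sample size section):

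n per arm = 2 × 0.12 × 0.88 × (1.96 + 0.8416)² / 0.05² = 0.2112 × 7.849 / 0.0025 ≈ 663.1, rounded up to 664.

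664 / 0.90 = 737.8, so 738 per arm and 1476 in total. This matches the article; allowing for the interim analyses it becomes 747 per arm. Nothing below changes it.

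**2. LOS: the sections side by side.**

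| Section | Content |
|---|---|
| Secondary outcomes | LOS is a count of days |
| Statistical methods | chi-squared and Fisher for qualitative variables; t-test or Wilcoxon for quantitative ones |
| Analysis of secondary endpoints | chi-squared or Fisher for LOS |
| Analysis of secondary endpoints | t-test or Wilcoxon for antibiotic-free days, also a day count |

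The LOS entry breaks the general rule and differs from the treatment of the other day count in the same section. No LOS categories are defined.

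**3. LOS: size of the loss.** The article gives no LOS distribution, so both models below are assumptions. Power is at two-sided 5%.

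*Model A:* 4 days plus a negative binomial (size 1), 747 per arm, day categories truncated at 16.

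| Mean excess days | Chi-squared | Rank-sum | Relative loss |
|---|---|---|---|
| 2.0 vs 1.6 | 57% | 85% | 1 − 57/85 = 33% |
| 2.0 vs 1.7 | 30% | 59% | 1 − 30/59 = 49% |

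Student's t-test reached 92% and 70% in the same two scenarios. With equal means, chi-squared and rank-sum each rejected in about 5% of trials.

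*Model B:* 3 days plus a negative binomial (dispersion 2), 664 per arm.

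| Mean days | Chi-squared | Rank-sum | Relative loss |
|---|---|---|---|
| 5.0 vs 4.8 | 13% | 39% | 1 − 13/39 = 67% |
| 5.0 vs 4.6 | 71% | 96% | 1 − 71/96 = 26% |
| 5.0 vs 4.5 | 93% | 99.8% | 1 − 93/99.8 = 7% |

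With no difference, rejection was 3.4% for chi-squared and 4.7% for rank-sum. The loss runs from 7 to 26 percentage points and is largest in relative terms when the true difference is small.

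*Order of days.* In one simulated data set, shuffling the day categories left the chi-squared p-value at 0.0043. Rank-sum on the same data gave 0.0008.

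**4. Signed-rank on independent arms.** With 664 against 660 patients the test could not be run. With equal arms, eight arbitrary re-pairings of the same data gave p-values from 0.0003 to 0.0026.

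**5. Flora and adequacy: order of events.** Common pre- and perioperative antibiotics, then surgery with its sample, then randomization, then the post-operative study drug. The Treatment administered section opens each arm's description by placing the preoperative doses after randomization, which conflicts with the Inclusion visit and Randomization sections. The regimen up to the end of the operation is the same in both arms, so allocation still cannot influence the sample. For flora, a 5% test therefore has a 5% false-positive chance and no treatment effect to find.

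For adequacy:
- If the therapy meant is the common regimen, adequacy is fixed before allocation and the flora argument applies.
- If it is the post-operative therapy, placebo patients receive none. A positive sample then has no drug to be compared with, while a negative sample counts as adequate although no drug was given. The comparison would mainly restate the allocation.

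**The case against.** **These are slips that the analysis plan will correct.** Signed-rank very likely is one: the endpoint-specific text says only Wilcoxon test, and the general rule also offers the t-test, which does fit independent arms. A reader might infer that every quantitative comparison is invalid; the article does not support that. The word is still wrong, and it is the only Wilcoxon variant named.

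**The LOS loss rests on assumed data.** This stands. Both arms receive three days of blinded injections, with discharge possible from day 4, so LOS may have little room to differ. Model A also makes no allowance for the planned 10% loss. A reader might infer that the LOS analysis loses most of its power. In Model A it keeps about two thirds or half; only the smallest difference in Model B goes beyond that. Nor does the test produce excess false positives.

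**Flora is only described.** The Secondary outcomes section does call the item a description, and the analysis section does not name the groups compared. But a chi-squared test of a listed secondary outcome in a two-arm trial implies a comparison of arms.

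**Adequacy is not clearly a pre-randomization variable.** This stands. A reader might infer that no treatment effect on adequacy is possible; that holds only under the common-regimen reading. The fault is an ambiguous definition.

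**Conclusion.** The point holds, at moderate weight and for secondary endpoints only. The primary analysis and the sample size are untouched.

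- **LOS:** a plain contradiction with the article's own rule. Day order and an estimate in days are lost. Power falls by about a third to a half under Model A and by 7% to 67% in relative terms under Model B; type I error is not inflated. The size depends on the assumed distributions and differences, the contradiction does not.
- **Signed-rank:** wrong for independent arms, probably a naming slip, with little consequence once corrected.
- **Flora:** a test between arms cannot show a treatment effect. This rests on the stated timing of sample and randomization.
- **Adequacy:** uninformative about treatment under one reading and not meaningful in the placebo arm under the other.

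**What to change.** 1. **LOS:** apply the article's rule for quantitative variables (Student's t-test or Wilcoxon rank-sum) and report the difference in mean days with its 95% confidence interval. A Hodges-Lehmann shift is not advised: in Model A, whole-day ties made the estimate 0 in all 100 trials checked per scenario, with interval [0, 0] in 99 of 100 and 100 of 100, although rank-sum often rejected.
2. **Statistical methods section:** replace signed-rank with rank-sum.
3. **Flora:** report by arm as a baseline description, without a significance test.
4. **Adequacy:** define it against the common pre- and perioperative regimen and report it the same way. No new subgroup analysis of the primary endpoint is needed.

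The cost is wording only. The Statistical methods section allows changes before unblinding with validation by the scientific advisory board. No extra data or patients are required.

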The biological sample collection performed in the context of this research was registered with the ANSM at the same time as the application for a clinical trial authorization. After termination of the study, storage of the biological sample collection will be registered with the French Ministry of Research and the Regional Health Agency (*Agence Régionale de Santé*). If the purpose of the research changes, approval from the CPP (IEC/IRB) will be requested.

## Discussion

In 2014, the world Health Organization published a report on the escalating global incidence of multidrug resistance caused by antibiotic overuse, which has become a significant threat to public health worldwide [28]. For example, antibiotic use is a risk factor for *Clostridium difficile* infections. In addition, prolonged antibiotic therapy after surgery can cause nausea, allergic reactions, and digestive complaints. Extended intravenous antibiotic prophylaxis leads to the prolongation of hospital stays and increased costs. There has thus recently been a tendency to minimize the use of postoperative antibiotics for uncomplicated appendicitis and anorectal abscesses [28, 29].

In this field, complicated appendicitis is a frequently occurring disease and accounts for 30% of all appendicitis cases. Thus, there is a real need to address this question. In this context, the first point to resolve was the definition of CAA, for which there are few data. St Peter et al. defined complicated appendicitis as appendicitis with a hole in the appendix or with fecaliths. This excluded abscesses and local peritonitis from the definition because the latter conditions were surprisingly associated with a lower rate of post-operative complications than the former (14% vs 18%, respectively) [8].

Another issue to resolve was the definition of localized peritonitis. We thus performed a study to evaluate how surgeons define localized and generalized peritonitis. In this study, we found that the best cut-off to distinguish localized from generalized peritonitis for surgeons was two quadrants. We also found that the overall concordance between surgeons and the initial operative report was 85% [10].

We also questioned the methodology and use of a placebo in the control group. This was requested by the national fund to limit the bias of the study. However, this increased the complexity of the protocol, as antibiotics and placebo must be prepared at the pharmacy for each patient and blinded from the patient and the surgeons. We first established that nurses should also be blinded. However, it was not feasible, as nurses are reluctant to inject medications prepared by another nurse.

In conclusion, the interest of post-operative antibiotic therapy in CAA is unknown. Therefore, the present trial is designed to evaluate whether a strategy with no post-operative antibiotics is not inferior to a strategy with post-operative antibiotic therapy on organ/space SSIs by POD 30.

## Data Availability

Data sharing is not applicable to this article as no datasets were generated or analyzed during the current study.
